## Abstract

**Introduction:**

Type II endoleaks (T2ELs) following endovascular aneurysm repair (EVAR) for abdominal aortic aneurysm (AAA) can lead to aneurysm growth, compromising the stent graft seal and risking rupture. Preventing these endoleaks during EVAR involves filling the AAA sac around the stent graft to exclude the aneurysm and block any arteries causing the endoleak. This study investigates the feasibility and safety of using AneuFix, a biocompatible injectable polymer developed by TripleMed (Geleen, the Netherlands), for aneurysmal sac filling during EVAR in high-risk T2EL patients.

**Methods and analysis:**

A feasibility, single-arm, single-centre clinical trial will initially include five patients with infrarenal AAA, eligible for EVAR, and at high risk for T2EL based on the number of patent lumbar arteries and the cross-sectional area of the aortic lumen at the level of the inferior mesenteric artery. Postevaluation by the Data Safety and Monitoring Board, the study cohort will extend to 25 patients. During EVAR and after stent graft deployment, the aneurysm sac is filled with AneuFix polymer using a filling sheath positioned parallel to the contralateral limb with the tip inside the aneurysm sac. Primary outcome is technical success (successful AAA sac filling). The secondary outcomes include clinical success at 6 and 12 months (occurrence of T2ELs and AAA growth assessed with CT angiography), intraoperative and perioperative complications, all endoleaks, adverse events, re-interventions, aneurysm rupture and patient survival.

**Ethics and dissemination:**

This trial was approved by the Dutch Authorities (Central Committee on Research Involving Human Subjects, IGJ), Amsterdam University Medical Centre Ethical Commission, and adheres to the Declaration of Helsinki and European Medical Device Regulation. Results will be shared at (inter)national conferences and in peer-reviewed journals.

**Trial registration number:**

NCT04307992.

STRENGTHS AND LIMITATIONS OF THIS STUDYAneuFix polymer is designed to be an easy-to-administer material for filling the abdominal aortic aneurysm lumen around the stent-graft during endovascular aneurysm repair.The injectable polymer can prevent type II endoleaks with a short additional procedure time.The feasibility trial contains no control group and the sample size is small.

## Introduction

Type II endoleak (T2EL) is caused by a retrograde blood flow from lumbar arteries or the inferior mesenteric artery (IMA) into the aortic abdominal aneurysm (AAA) sac after endovascular aneurysm repair (EVAR). It occurs in 18%–30% patients treated with EVAR.^1^,^5^ A large fraction will resolve spontaneously over time however 15%–35%^4^,^6^ of the patients with persistent T2EL are at risk for continuous AAA growth which can compromise aortic seal zones (proximal or distal) and might eventually cause aortic rupture in 2%.^4^

## Background and relevant literature and data

In order to prevent T2EL, several AAA sac management strategies are being developed and implemented worldwide. Pre-emptive embolisation of aneurysm sac side branches with coils can be effective, but requires a significant learning curve, requires an additional procedure and is time consuming.^6^,^10^ Another strategy is intraoperative prophylactic AAA sac filling. The aneurysm sac can be filled with an embolisation material (coils and/or liquid) during EVAR after which the aneurysm sac is embolised.^11^,^17^ Furthermore, endovascular aneurysm sealing (EVAS) has been, for a short period of time in the past, widely performed, however, a device recall decreased the implantations significantly.^18^

The crucial difference between EVAR with active sac filling and EVAS is the approach to sealing the aneurysm and stent-graft fixation. EVAS does not involve fixation above or below the aneurysm. Instead, it focuses on sealing off the aneurysm sac itself using polymer-filled endobags that conform to the sac shape. In contrast, EVAR with active sac filling uses a standard EVAR stent graft, which achieves proximal and distal seal above and below the aneurysm in relatively healthy aortoiliac tissue, effectively isolating the aneurysm from blood flow. Adjacent to this, the AAA sac is filled around the standard EVAR stent graft.

In recent years, a novel embolic material was developed specifically for AAA sac filling during EVAR; AneuFix (TripleMed, Geleen, the Netherlands) injectable polymer.

In this study, we will investigate the feasibility and safety of AneuFix use for aneurysm sac filling during EVAR in patients with high risk of T2EL.

## Methods and analysis

### AneuFix biocompatible injectable polymer

AneuFix is a two-component injectable polymer, based on polydimethylsiloxane which is widely applied for long-term implants such as dental and bone because of its biological inertness and stability.^19 20^ It is a medical implant which has the unique properties to change viscosity during the procedure, from low viscosity (tooth-paste like) during injection to high viscosity after injection and after 2 min cures to a flexible, solid and compliant implant. AneuFix has been extensively studied in preclinical tests and demonstrated to be biocompatible, biostable and has a thrombogenicity comparable to expanded polytetrafluorethylene; a material used widely in current aortic stentgrafts.^20 21^ Before clinical application, to prove feasibility and safety several in vitro and in vivo experimental studies with AneuFix have been conducted and published.^20^,^25^ Recently, we published our initial experience and short-term results of T2EL treatment with AneuFix, for patients with AAA growth with T2EL after EVAR during follow-up.^26^

The AneuFix-kit contains a double-barrel 2×20 mL syringe with the polymer, a dispenser gun and a static mixer which is mounted onto the dispenser (figure 1A,B). During injection, both components are mixed in the static mixer through a plastic helix, after which the curing process starts. AneuFix contains 30% tantalum, to ensure real-time visualisation under fluoroscopic guidance.

**Figure 1 F1:**
[figure not shown]
Dispenser for injection with static mixer (**A**) and syringe with AneuFix material (**B**).

The implant was classified as a class III medical device. In the European Union, these medical devices require CE certification by the notified body before introduction into the market. AneuFix is pre-CE mark and will go for registration after enough patients are treated during the pilot phase.

### Study objectives

To investigate the safety and feasibility of prophylactic aortic aneurysm sac filling with AneuFix injectable polymer during EVAR in patients at high risk for T2EL, as defined in the inclusion criteria.

### Study design

This is a feasibility, single-arm, single-centre clinical trial. Initially, a pilot study will be performed with five patients. The Data Safety and Monitoring Board (DSMB) will extensively evaluate the procedure imaging, clinical data and outcome after the second, fourth and fifth patients are treated. If safety and feasibility are confirmed by the DSMB, the total cohort will be expanded to 25 patients. After the pilot study and subsequent DSMB evaluation, the remaining 20 patients will be treated. Figure 2 displays the study design.

**Figure 2 F2:**
[figure not shown]
Overview of study follow-up. CTA, CT angiography; EVAR, endovascular aneurysm repair; FU, follow-up; PSF, prophylactic sac filling.

### Primary endpoint

#### Technical success

Technical success defined as successful AAA sac filling during EVAR.

### Primary safety endpoints

#### Adverse events

Incidence of (serious) adverse events (SAEs) and adverse device effects, both intraoperatively and during follow-up, related to AneuFix and the procedure (online supplemental material 1 for full definitions).

#### Perioperative complications

The rate of any complications occurring within the first 30 days post-EVAR with AneuFix.

#### Aneurysm rupture

The rate of aneurysm rupture occurring during the inclusion period.

#### Patient survival

The proportion of patients surviving, and overall clinical outcome, assessed throughout the study up to 24 months.

### Secondary endpoints

#### Clinical success

Clinical success defined as the occurrence of T2ELs and aneurysmal sac growth, as assessed at both 6 and 12 months following the EVAR procedure, and confirmed through CT angiography (CTA).

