### Assessments and follow-up

#### Screening assessments

Demographic data, relevant medical history, comorbidities are gathered from the electronic patient record file. The AAA volume and sac anatomy are determined from preoperative CTA (<90 days old). Relevant data on current medication, estimated glomerular filtration rate and serum creatinine is gathered. If all the inclusion and none of the exclusion criteria are met, patients will be considered for the procedure.

Furthermore, according to the protocol inclusion criteria (version 1.7), all patients are screened for high risk of T2EL development; the amount of patent lumbar arteries is measured on preoperative CTA and the CSA of the aortic lumen at the level of the IMA.

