#### Postprocedure until hospital discharge

Within the first 24 hours, and prior to patient discharge, CTA is performed to evaluate the appropriate filling of the aneurysm sac and absence of T2ELs. Adverse events are recorded if present. Also, postprocedural medication is recorded, C reactive protein is assessed.

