#### 6-months follow-up

CTA imaging (blank, arterial, venous with scatter reduction) is performed to determine clinical success at 6-months follow-up ±30 days. Any medication change will be registered and any adverse events.

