The DSMB is an independent group consisting of expert clinicians, who collectively have experience in the management of patients with abdominal aneurysm treatment and in the conduct and monitoring of clinical trials. The DSMB members have been selected by the sponsor, after consultation with the clinical trial investigators. The DSMB is responsible for oversight of study safety considerations and for safeguarding the safety of clinical trial population through assessment of the trial safety data. On the basis of their review, the DSMB can conclude one of the following actions: continue, modify or discontinue the study.

A validated electronic data collection system (eCRF) will collect the clinical data (Castor EDC, XX). A GDPR-validated transmission system will be implemented to transfer the data to the core laboratory and DSMB for further assessment. An independent radiologist will function as imaging corelab. Patient imaging will be assessed on AAA diameter (multi-planar reconstruction, double oblique measured) and presence of possible subsequent endoleak (all types).

A clinical monitoring plan, based on risk assessments and focussed on the primary and on the secondary objectives, is in place at the sponsor’s site. This will be executed during the conduct of the study. Clinical data should be retained at the site for 15 years and at the sponsor’s premises for a minimum of 2 years after completion of the clinical study. Trial data can be accessed upon request.

Dissemination of the feasibility trial results will be achieved through submission to international peer-reviewed journals and presentations at international conferences.

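### Clinical success is defined as the occurrence of the two events the device should prevent, and reversing the sense leaves patients with only one event unclassified

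*Protocol article*

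**What the plan says.** Under Secondary endpoints, Clinical success, the protocol article states: "Clinical success defined as the occurrence of T2ELs and aneurysmal sac growth, as assessed at both 6 and 12 months following the EVAR procedure", confirmed by CT angiography (CTA). The abstract's Methods and analysis paragraph has the same direction and the same conjunction: "clinical success at 6 and 12 months (occurrence of T2ELs and AAA growth assessed with CT angiography".

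Three other places show which direction is wanted or where the term is used:

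- Abstract, Introduction, on the purpose of sac filling: "Preventing these endoleaks during EVAR involves filling the AAA sac around the stent graft".
- Postprocedure until hospital discharge: "CTA is performed to evaluate the appropriate filling of the aneurysm sac and absence of T2ELs".
- 6-months follow-up: CTA "is performed to determine clinical success at 6-months follow-up". The 12-months follow-up section says the same for its visit. Neither restates the definition.

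The core-lab description in Ethics and dissemination has diameter and endoleak read as two items and gives no rule for combining them into success or failure.

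**The concern.** The definition runs the wrong way. It names as success the two findings that the intervention is meant to prevent. The error appears in both places that define the endpoint, and the sections that rely on the term do not repair it.

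A reader will probably reverse the sense in their head, but that exposes a second problem. The opposite of *T2EL and growth* can be *not both together* or *neither one*. These differ for a patient with an endoleak and a stable sac, and for a patient with a growing sac and no visible endoleak. In a single-arm study of 25 patients reported as proportions, a few such patients change the success rate noticeably. Clinical success is also the only listed endpoint that contains sac growth, which the article itself names as the route to loss of seal and rupture.

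**Working it through.** The plan gives no figure that depends on this definition, so there is nothing to reproduce. The check is a truth table followed by an illustration of size.

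**Step 1. Classify the four kinds of patient under three readings.**

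A = literal text (success if T2EL and growth). B = simple negation (success unless both occur). C = freedom from each (success only if neither occurs).

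| T2EL | Growth | A | B | C |
|---|---|---|---|---|
| no | no | not success | success | success |
| no | yes | not success | success | failure |
| yes | no | not success | success | failure |
| yes | yes | success | failure | failure |

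Reading A is the reverse of the trial's aim in the first and last rows. Readings B and C agree on those two rows and disagree on both middle rows.

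**Step 2. Inputs for the illustration.**

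- *t*, T2EL rate after EVAR: 18% to 30% (main Introduction).
- *g*, share at risk of continuing growth: 15% to 35% (main Introduction, stated for persistent T2EL; applied here to all T2EL).
- N = 25 (Sample size determination).
- Assumption: growth occurs only in patients with T2EL.

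**Step 3. Formulas.**

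- Both events: *t* × *g*. This is also the literal success rate (A).
- Success under B: 1 − *t* × *g*.
- Success under C: 1 − *t*.
- Patients on whom B and C disagree: *t* − *t* × *g*.

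**Step 4. Results for every combination.**

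| *t* | *g* | A | B | C | B and C disagree | of 25 |
|---|---|---|---|---|---|---|
| 0.18 | 0.15 | 2.7% | 97.3% | 82% | 15.3% | 3.8 |
| 0.18 | 0.35 | 6.3% | 93.7% | 82% | 11.7% | 2.9 |
| 0.30 | 0.15 | 4.5% | 95.5% | 70% | 25.5% | 6.4 |
| 0.30 | 0.35 | 10.5% | 89.5% | 70% | 19.5% | 4.9 |

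The same patients therefore give a success rate of 89.5–97.3% under B and 70–82% under C. The gap is 11.7 to 25.5 percentage points.

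**The case against.** The strongest reply is that the intent is obvious. The aim is prevention, the discharge CTA looks for absence of endoleak, and nobody would report an endoleak with a growing sac as a success. The sentence may be a loose list of components, and the full Clinical Investigational Plan (version 1.7), which is not shown, may word it properly. The endpoint is secondary, summarised as a proportion, with no stated test and no stated link to the sample size. This reply stands as far as severity goes. It does not remove the defect: the article states the rule, states it the wrong way round twice, and even the obvious intent does not settle the single-event patients.

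The illustration is also open to challenge. The rates describe general EVAR patients, whereas this cohort is selected for high risk and then treated to lower that risk. The growth figure is given for persistent T2EL only, and the article says that many endoleaks resolve. The size in this trial is therefore uncertain in both directions; the ambiguity is not.

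Several stronger readings are tempting and should not be drawn:

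- *A patient with an endoleak and no growth passes as a success under the text.* Taken literally, that patient is not a success; this happens only under reading B.
- *This is the only efficacy endpoint.* All endoleaks and re-interventions are separate secondary endpoints, so such a patient's endoleak would still be reported.
- *Growth has two conflicting metrics.* The core lab has one: "Patient imaging will be assessed on AAA diameter (multi-planar reconstruction, double oblique measured". The volume in Screening assessments ("The AAA volume and sac anatomy are determined from preoperative CTA (<90 days old") describes preoperative anatomy and is not tied to growth.
- *Failure may have to be present at both visits.* The two follow-up sections each determine clinical success at their own visit.
- *A patient re-treated for T2EL counts as a success at 12 months.* The article has no rule on this. That rule and the baseline for growth are details it may leave to the full plan.

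**Conclusion.** The point holds in two parts. First, the published definition of clinical success is inverted in both the endpoint section and the abstract, contradicts the trial's purpose, and is not corrected elsewhere. This needs no assumption. Second, once the direction is corrected, the conjunction leaves patients with T2EL only or growth only unclassified.

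The size quoted for the second part, disagreement on 2.9 to 6.4 of 25 patients, is an illustration. It rests on general EVAR rates, on applying the growth share for persistent T2EL to all T2EL, and on growth never occurring without T2EL. If growth also occurred without T2EL, those patients would add to the disagreement.

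Severity is moderate: the rule is wrong as written and decides a reported result, but the endpoint is secondary and descriptive.

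**What to change.** In the Clinical success section and in the abstract, replace the definition with: *Clinical success at 6 months and, separately, at 12 months = absence of T2EL and absence of aneurysm sac growth on core-lab-read CTA; either event is failure.* Report the two components separately as well, so that readers can see how many patients had one event only.

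Nothing else needs to enter the composite; re-intervention, conversion and rupture already have their own endpoints. The cost is wording only. The CTAs at 6 and 12 months and the core-lab readings of diameter and endoleak are already planned. The reported success rate may be less favourable than under the *not both* reading.

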#### All endoleaks

Occurrence of any type of endoleaks (I–IV) during the complete inclusion period as confirmed on CTA imaging.

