#### Re-interventions

The rate of secondary endovascular or surgical re-interventions, including the rate of conversion to open AAA repair.

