#### 12-months follow-up

CTA imaging (blank, arterial, venous with scatter reduction) is performed to determine clinical success at 12-months follow-up (±30 days). Any medication change will be registered and any adverse events.

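### Clinical success is determined only by the 6- and 12-month CTAs, so a patient re-treated or converted to open repair before a scan can count as a success at that scan

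*Protocol article*

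**What the plan says.** The Protocol article, Secondary endpoints, Clinical success, gives two components: "Clinical success defined as the occurrence of T2ELs and aneurysmal sac growth". It gives two assessment times and one method: "as assessed at both 6 and 12 months following the EVAR procedure, and confirmed through CT angiography (CTA". I read the definition as the absence of both findings; its wording is inverted, but that is a separate matter.

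The follow-up sections tie the endpoint to the scheduled scans. At 6 months, CTA "is performed to determine clinical success at 6-months follow-up ±30 days". At 12 months, CTA "is performed to determine clinical success at 12-months follow-up (±30 days".

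Three related items stand apart from clinical success:

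- Re-interventions (secondary endpoint): "The rate of secondary endovascular or surgical re-interventions, including the rate of conversion to open AAA repair".
- All endoleaks (secondary endpoint): any endoleak type, "during the complete inclusion period as confirmed on CTA imaging".
- Aneurysm rupture (primary safety endpoint): a rate over the inclusion period.

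The section on the period up to discharge adds an early scan: "CTA is performed to evaluate the appropriate filling of the aneurysm sac and absence of T2ELs". That scan does not enter clinical success. No section says that a re-intervention, conversion or rupture makes a patient a clinical failure.

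**The concern.** Sac filling is meant to prevent T2EL and the growth that can follow it. A patient who needed further treatment for either, or who lost the endovascular repair altogether, has not had that benefit. If success is only what the scheduled scan shows, effective re-treatment turns such a patient into a success. After conversion to open repair no excluded sac is left to leak or grow, so the definition yields either a success or a missing value, and the text does not say which.

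The trial has no control group. Readers will look to the 6- and 12-month clinical success proportions for the first sign of whether filling works. A definition that can move failures into the success count shifts those proportions in one direction only.

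**Working it through.** **Step 1: what the definition does with each patient.** Two readings of the text are possible: status at each scan, or a cumulative record over the two scans.

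| Course | Status at each scan | Cumulative over both scans |
|---|---|---|
| T2EL treated before the 6-month scan, both scans clean | success at 6 and 12 months | success |
| T2EL on the 6-month scan, treated, 12-month scan clean | failure at 6, success at 12 months | failure |
| T2EL first found after the 6-month scan, treated, 12-month scan clean | success at 6 and 12 months | success |
| Conversion to open repair before the 6-month scan | success or missing | success or missing |

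The status reading fits the text better. The follow-up sections let each scan determine clinical success at its own visit, and the article uses whole-period wording for All endoleaks but not here. The gap remains under either reading; the cumulative one closes only the second row.

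**Step 2: size per patient.** The article states no figure for clinical success, so there is nothing to reproduce. The only input from the document is N = 25 (Sample size determination). Let

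- F = patients who are failures under a rule that counts the events above;
- k = those among F who were re-treated or converted before the scan and whose scan, if done, is clean.

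Then

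- events counted as failure: (25 − F)/25;
- scan only, the k patients scored as successes: (25 − F + k)/25;
- scan only, the k patients dropped as missing: (25 − F)/(25 − k).

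The second exceeds the first by k/25, which is 4 percentage points per patient whatever F is. The third also exceeds the first whenever k > 0 and F < 25, by somewhat less.

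**Step 3: illustration.** F and k are assumptions. For scale, the Introduction's general post-EVAR T2EL rate of 18%–30% would give 25 × 0.18 = 4.5 to 25 × 0.30 = 7.5 patients. It is not a rate for this high-risk cohort or for filled sacs. I take F = 5 and F = 8.

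| F | k | Events counted as failure | Scored as success | Dropped |
|---|---|---|---|---|
| 5 | 1 | 20/25 = 80% | 21/25 = 84% | 20/24 = 83.3% |
| 5 | 2 | 20/25 = 80% | 22/25 = 88% | 20/23 = 87.0% |
| 5 | 3 | 20/25 = 80% | 23/25 = 92% | 20/22 = 90.9% |
| 8 | 1 | 17/25 = 68% | 18/25 = 72% | 17/24 = 70.8% |
| 8 | 2 | 17/25 = 68% | 19/25 = 76% | 17/23 = 73.9% |
| 8 | 3 | 17/25 = 68% | 20/25 = 80% | 17/22 = 77.3% |

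Exact (Clopper-Pearson) 95% intervals put this in proportion: 20/25 gives 59.3% to 93.2%, and 22/25 gives 68.8% to 97.5%. The shift is smaller than the sampling uncertainty, but it is systematic and upward.

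**The case against.** **The events are reported anyway.** Rupture is a primary safety endpoint, conversion is named under Re-interventions, and All endoleaks covers any leak confirmed on CTA over the whole period. This stands: a reader might infer that the worst failures vanish from the trial, and they do not. But separate counts do not correct the clinical success proportion, nor show which successes had been re-treated.

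**The gap is narrow.** A T2EL on the 6-month scan is recorded as a failure at 6 months. Between the pre-discharge CTA and month 6 the only planned contact is at 1 month, with no imaging mentioned, so a leak treated before month 6 must come from the early scan or an unscheduled one. This also stands. It limits how many patients are affected, not how each is scored.

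**Early leaks that close by themselves.** Because the Introduction says of T2EL that "A large fraction will resolve spontaneously over time", a reader might infer that spontaneous closure before month 6 inflates success further. The documents do not support that. The Introduction places the growth risk in persistent T2EL, so assessing at 6 and 12 months is a defensible choice. An early leak is picked up by the pre-discharge CTA and All endoleaks, and an untreated leak that closed would remain a success under the amended rule.

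**This belongs in the full plan.** The article is condensed; the full clinical investigation plan or an analysis plan, neither shown, may hold a handling rule. That is fair for missing scans in general. What counts as success, however, belongs to the endpoint definition, and the article fixes its components and timing without these events.

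**No efficacy claim is planned.** The objective is safety and feasibility, the analysis is descriptive, and the missing control group is disclosed. This lowers the weight of the point but does not remove it.

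**Conclusion.** The point holds in limited form. As written, a patient with a re-intervention for T2EL or sac growth, or with a conversion, before a scan can count as a clinical success or go missing at that time point. One whose T2EL was seen at 6 months and then treated is still a 6-month failure and can be only a 12-month success.

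The overstatement is 4 percentage points per patient scored as a success, out of 25. The total depends on a number the documents do not give: an assumed 1 to 3 patients gives 4 to 12 points. A reader might take that range as an estimate of bias in this trial; it is arithmetic on an assumption, and with no such patient the bias is zero.

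This is a secondary, descriptive endpoint in a feasibility study. The definition should be corrected; the primary endpoint is not touched.

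**What to change.** Add to the definition of clinical success:

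- A patient who has had a re-intervention for T2EL or sac growth, a conversion to open repair, or an aneurysm rupture before a time point is a clinical failure at that and every later time point, whatever the CTA shows.
- All treated patients stay in the denominator, so a patient with no evaluable scan because of such an event is counted as a failure and not dropped.

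This is a scoring rule only and changes nothing in patient care. It costs two sentences. Re-interventions, conversions and ruptures are already endpoints, so no new data, visit or patient is needed. The downside is a slightly less favourable success rate if such events occur.
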